*Process evaluation:* Process evaluation data will be synthesized to produce an overall summary of the outcomes of the process evaluation, and this will be supplemented with other outcomes data. NONs will be transcribed. IDIs are audio-recorded and transcribed/translated into English, where applicable. A common data analysis plan will be used that describes the synthesized analysis of the data. It enables evaluation at a country level and comparability across countries. This is necessary to be able to answer questions about the intervention and its effects. All qualitative components will be analyzed in a single qualitative data analysis database using NVivo, a qualitative analysis software. Data will be thematically coded at country level, although a single yet iterative code list will be used to enable cross country comparisons where applicable. Throughout analysis of the process evaluation data, research questions may be identified to be explored in the process evaluation. The case studies of change can be used to consolidate and synthesize data, providing information on case studies of interest (e.g., high performing in comparison to low performing sites or facilities). Document review, which comprises collecting materials or forms of documentation, might be useful to help develop the case studies of change. 

7
Ethics

CaPSAI Project master and country protocols (Project ID A65896) were approved by technical and ethics review committees at the World Health Organization (WHO). Additionally, the country protocols were reviewed and approved by the Population Council Institutional Review Board (exemption approval - # EX201714) and Ghana Health Service Ethics Review Committee (GHS-ERC:009/08/2017) in Ghana. In Tanzania, the protocol has been approved by Ifakara Health Institute Institutional Review Board (IHI/IRB/No:18-2018 and IHI/IRB/AMM/No:03-2019) and the National Institute of Medical Research (NIMR) review board (NIMR/HQ/R.8a/Vol.IX/2668), as well as the NIMR/Mbeya Medical Research and Ethics Review Committee (GB.152/377/01/214a).

The study adheres to the highest ethical standards, and to the current international and local legislation pertaining to research governance. All study participants undergo informed consent procedures. For low literacy respondents expressing interest in participating in the study, the data collector requests the respondent to identify a trusted literate witness to be part of the informed consent process or to come back to the facility with the trusted literate witness to go through the consent. For adolescents, the consenting/assenting and interviewing may a be a two-step process. The researcher explains the study and informs the adolescent that their parent or guardian needs to be informed about the study and give their consent unless they are emancipated adolescents. If the adolescents agree to participate and they are accompanied by their parents or guardian, consent is obtained from the parents/guardian, followed by assent from the adolescent. If the parent/guardian is not present at the facility, they are invited to come back to the facility with their parent/guardian to go through the consent and assent process separately. Emancipated adolescents are able to give informed consent in both countries according to local regulatory bodies. Written informed consent is not taken for the non-participant observation but a group consenting process is followed. Participants are provided with a copy of a study information sheet (see CaPSAI Informed Consent Forms-
*Extended data*)
^42^, informed that the activity is part of a research study and are offered the opportunity to leave (to opt-out of being observed) or to ask questions about the study aspects. 

All identifying information is removed from transcripts and stored separately with access restricted to the research team. All transcripts are stored electronically in password-protected online services, and physical documents are securely stored at the principal investigators’ institutions.

8
Dissemination

The study results will be disseminated in participating districts and at the national level as well as with the global FP/C communities through publications and presentations to contribute in addressing the gap in evidence on integration and measurement of social accountability interventions for FP/C. An implementation manual providing guidance on social accountability for FP/C will be developed based on the findings of the study.

De-identified country-specific data will be available one year after primary manuscripts have been published as agreed on a Data Transfer Agreement. De-identified country-specific data will be available for 10 years after that. As this is a multi-country study, the ownership of country-specific data will be at country-level. Request for de-identified data may be submitted to Primary Sponsor (WHO SRH/HRP Research) or Principal Investigators, and data will be shared contingent on approval by the internal review and approval by local internal ethics review board.

9
The CaPSAI Project team

The study and intervention design were jointly conceptualized and designed by the Department of Sexual and Reproductive Health and Research, WHO, which includes the United Nation Development Program/United Nations Population Fund/United Nations Children’s Fund/WHO/World Bank Special Programme of Research, Development and Research Training Human Reproduction (WHO SRH/HRP) and the Evidence Project. Overall oversight for the CaPSAI is the responsibility of WHO SRH/HRP. WHO SRH/HRP is leading the research component.

Population Council in Ghana and Ifakara Health Institute (IHI) in Tanzania were selected to conduct the research study based on the strength of experience and expertise of the Principal Investigator and the existing infrastructure, capabilities and stellar track record. Ghana Integrity Initiative (GII), which is the Local Chapter of Transparency International (TI) in Ghana, and Sikika in Tanzania were the national CSOs selected to implement the intervention based on their previous experience of conducting social accountability interventions in health.

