*Contraceptive uptake:* For sample size calculations, it is assumed that, at pre-intervention, the mean number of new users per facility per month would be similar in both the intervention and control arms. It is further assumed that in the control arm, the pre-test and post-test mean number of new users per facility per month, per arm will remain the same. Study sample size and power were estimated in two ways: with the facility as the unit of measurement for Poisson regression, and with the monthly data points as the unit of measurement for time series regression. With the facility as the unit of sampling and of analysis, and assuming two-time points of interest, at pre-test (or baseline) and at post-test, different sample size estimates were computed using a two-sided t-test with Type I error at 5% level, statistical power at 80%, and assuming equal variance. These various sample size estimates are provided assuming a constant denominator (included as an offset in the Poisson model) and a pooled variance for mean number of new users at pre-intervention in both arms of between 100 and 200 new users per facility, per month, and a difference in uptake per facility per month, at post-intervention of between 60 and 200 new users. Approximately, five to eight facilities are needed per intervention or control group to detect an approximately two-fold increase in the rate of new users with 80% power and allowing for a 5% Type I error. The monthly data points were used as the unit of analysis and, based on effect size and time periods, the simulation-based power calculation provided by Zhang
*et al.*, 2011
^39^ was used. Assuming an effect size of 2.0 (derived from 100 new users in control group and 200 new users in intervention group and a pooled standard deviation of 50) and an autocorrelation of up to 0.3, a total of 12 data points – the equivalent to six monthly pre-intervention data points and six monthly post-intervention data points – would be needed to achieve 80% power at p=0.05 statistical significance level
^39^.ii. 

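### The facility-level sample size for contraceptive uptake prints a pooled variance of 100 to 200, which gives two or three facilities per arm, not the stated five to eight

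*Protocol article*

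**What the plan says.** The text is in the protocol article, Study design and methods, item 4 (Sample size), part i (Contraceptive uptake). Two calculations are given.

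**Facility-level method.** The facility is the unit: "With the facility as the unit of sampling and of analysis". Estimates were computed "using a two-sided t-test with Type I error at 5% level, statistical power at 80%, and assuming equal variance". The spread is given as "a pooled variance for mean number of new users at pre-intervention in both arms of between 100 and 200 new users" per facility per month. The effect is given as "a difference in uptake per facility per month, at post-intervention of between 60 and 200 new users". No change is expected in the control arm. The conclusion is that "five to eight facilities are needed per intervention or control group to detect an approximately two-fold increase in the rate of new users".

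**Monthly time-series method.** The unit is the monthly data point, and the effect size of 2.0 is "derived from 100 new users in control group and 200 new users in intervention group and a pooled standard deviation of 50".

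The study setting section selects eight intervention and eight control facilities in each country. Table 4 names contraceptive uptake among the primary outcomes.

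**The concern.** The printed variance is too small to lead to five to eight facilities per arm for any difference in the listed range. It is also given in new users, whereas a variance would be in squared units, so the label itself is doubtful. The monthly method, a few lines further on, uses an SD whose square is 12.5 to 25 times the printed variance.

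The number of facilities fixes the size of the uptake comparison. Depending on what 100 to 200 stands for, eight per arm is far more than needed, about right for a doubling from 100, or well short of it. The target effect is stated, but the spread that supports it is not recoverable from the text. A reader therefore cannot judge what a null result on uptake would exclude.

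**Working it through.** **Inputs from the sample size section.** Two-sided two-sample t-test, α = 0.05, power 0.80, equal variance; variance 100 to 200; difference Δ = 60 to 200; stated result n = 5 to 8 per arm. Equal arms follow from eight versus eight. From the monthly method: means 100 and 200, SD 50.

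**Formula.** With n facilities per arm and between-facility SD σ, the non-centrality is δ = Δ / (σ√(2/n)) with 2n − 2 degrees of freedom. Power is the probability that the non-central t exceeds the two-sided 5% critical value. The required n is the smallest that gives at least 80%.

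**1. The monthly method's effect size.** (200 − 100)/50 = 2.0, as stated. The corresponding variance is 50² = 2,500, which is 2,500/200 = 12.5 to 2,500/100 = 25 times the variance printed for the facility-level method.

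**2. The facility-level figure with the printed variance.** √100 = 10 and √200 = 14.1.
- Variance 100, Δ = 60, n = 2: δ = 60/(10 × 1) = 6.0, power 84%. Two per arm suffice.
- Variance 200, Δ = 60, n = 2: δ = 60/14.14 = 4.24, power 61%. With n = 3: δ = 60/(14.14 × 0.816) = 5.20, power 97%. Three per arm are needed.
- Δ = 100, n = 2: power 99% (variance 100) and 92% (variance 200). Two per arm suffice. The same holds for Δ = 200.

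The printed inputs thus give 2 to 3 per arm, and the stated 5 to 8 is not reproduced. Other standard variants do not recover it. A one-sided test gives 2. A difference in differences with independent pre and post values (variance doubled) gives 2 to 4. Treating 100 to 200 as a Poisson mean gives about 1 by the normal approximation.

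**3. If 100 to 200 is a mislabelled SD.** Required n per arm:

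| Difference | SD 100 | SD 200 |
|---|---|---|
| 60 | 45 | 176 |
| 100 | 17 | 64 |
| 150 | 9 | 29 |
| 200 | 6 | 17 |

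Five to eight appears only in the corner with the smallest SDs and the largest differences. At SD 100, eight per arm detect about 151 or more. At a difference of 200, five to eight corresponds to SDs of about 99 to 133. A difference of 200 is a two-fold rise only from a baseline of 200.

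**4. What SD makes five to eight fit a rise from 100 to 200?** Setting power to 80% at Δ = 100 gives σ = 49.4 for n = 5 and 66.4 for n = 8, a variance of about 2,400 to 4,400.

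**5. What eight per arm detect at two candidate SDs.** With n = 8, √(2/8) = 0.5.

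| SD | Difference | δ | Power |
|---|---|---|---|
| 50 | 100 | 100/25 = 4.0 | 96% |
| 50 | 75 | 75/25 = 3.0 | 80% |
| 50 | 60 | 60/25 = 2.4 | 61% |
| 100 | 200 | 200/50 = 4.0 | 96% |
| 100 | 100 | 100/50 = 2.0 | 46% |

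At SD 50 a difference of 100 needs 6 per arm (79% power with 5), and a difference of 60 needs 12.

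**The case against.** The strongest defence is that this is a labelling slip. The stated target, an approximately two-fold increase, is clear, and the monthly method spells it out as 100 versus 200. At an SD near 50, six facilities per arm meet it and eight give 96% power. The two methods also have different units of analysis, so the spread between facilities need not equal the SD of monthly data points, and a gap between the two is not in itself a contradiction. Both points stand. They limit the consequence, but they do not make the printed variance yield five to eight facilities.

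Two stronger readings are tempting, and the article supports neither.

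- A reader might infer that the stated inputs fail to cover a difference of 60, and that the article claims sensitivity it lacks. With the printed variance, two or three facilities already detect 60. A shortfall appears only if SD 50 is borrowed from the monthly method, or if 100 to 200 is read as an SD. The article ties five to eight facilities to a two-fold increase; 60 is only the lower end of the range over which estimates were computed.
- A reader might infer that SD 50 must be the figure behind five to eight. It is a plausible source, but SD 100 with a difference of 200 also gives 6 per arm and lies within the listed ranges if 100 to 200 is an SD. The text does not settle which was used.

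**Conclusion.** The point holds as an error in the printed inputs. A pooled variance of 100 to 200 gives 2 to 3 facilities per arm over differences of 60 to 200, and the stated 5 to 8 does not follow. Depending on the reading, the requirement for a rise of 100 is 2 per arm (variance as printed), 6 (SD 50), or 17 to 64 (SD 100 to 200).

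The first result rests only on the article's own inputs and the t-test it names. The figures for SD 50 and SD 100 are conditional: the between-facility SD actually used is not given, and SD 50 belongs to a different unit of analysis. The finding does not show that eight facilities per arm are too few. If the between-facility SD is no more than about 66, eight per arm have at least 80% power for a rise from 100 to 200.

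**What to change.** In the facility-level calculation:

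1. Say whether 100 to 200 was a variance, an SD or a mean, and replace the phrase with the between-facility SD actually used.
2. Reconcile that SD with the five to eight facilities, stating the baseline and difference meant by a two-fold increase. Say how it relates to the SD of 50 in the monthly method.
3. Restate what eight facilities per arm detect at that SD. If SD 50 applies: 96% power for a difference of 100, 80% for about 75, 61% for 60. If SD 100 applies: 46% for 100 and 96% for 200.

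Only the authors can say which spread was used, so the replacement figures must come from their calculation. The cost is a corrected phrase and a few restated figures; the number of facilities does not need to change.

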*Contraceptive uptake:* All potential confounders associated with all the facilities enrolled are recorded. An ITS segmented Poisson regression model will be used to estimate both the level changes in first-use modern contraception rate and changes in time trends for the rate of modern contraception first-use rates per 10,000 women-months, after the introduction of the intervention. The generalized estimating equation (GEE) Poisson segmented regression model will allow adjustment for correlation due to repeated observations from the same facilities, while also adjusting for important baseline family planning facility characteristics. ii. 
*Contraceptive use:* For categorical variables frequencies and percentages will be reported, and for quantitative variables number of subjects, means, standard errors, medians, interquartile range, minima, and maxima will be reported. Rate of loss to follow-up for the one-year follow-up period will be computed by intervention arm. The one-year cumulative method discontinuation and method switching rates will be compared between the intervention and control arms. Because of the clustered nature of the outcomes, with intervention package designed at the cluster level, all time-to-event outcomes including loss to follow-up, method discontinuation, and method switching, will be analyzed with hazard ratios estimated from the marginal Cox model and/or shared Frailty models. The model will be adjusted for baseline potential confounders at participant and/or facility level. Two-sided tests, 5% significance levels and 95% confidence intervals will be used for all relevant parameters. Statistical Analysis System (SAS) Version 9.4 and R Version 3.3.3 software packages will be used for the statistical analyses. Open-ended questions will be listed and coded for meaningful comparisons of their distribution.iii. 

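### The 12-point, 80% power statement for contraceptive uptake does not match the controlled, segmented, facility-level analysis that the protocol plans

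*Protocol article*

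**What the plan says.** In the protocol article, Study design and methods, 4 Sample size, i, power for uptake is estimated in two ways. One takes the facility as the unit. The other is framed "with the monthly data points as the unit of measurement for time series regression" and is the subject here.

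- Effect: "Assuming an effect size of 2.0 (derived from 100 new users in control group and 200 new users in intervention group", with a pooled SD of 50.
- Points and correlation: "an autocorrelation of up to 0.3, a total of 12 data points", split as "six monthly pre-intervention data points and six monthly post-intervention data points".
- Result: these points "would be needed to achieve 80% power at p=0.05 statistical significance level". The figure is taken from a cited simulation study whose model the article does not describe.
- Scale: the same paragraph works in counts per facility per month. It assumes that before the intervention "the mean number of new users per facility per month would be similar in both the intervention and control arms", and that the control mean then stays unchanged.

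The analysis is described elsewhere. Under 6 Data analysis, i: "An ITS segmented Poisson regression model will be used to estimate both the level changes in first-use modern contraception rate", together with changes in time trend, by GEE to allow for repeated observations on each facility. Under 3 Study design, i, the design is an interrupted time series with a control group, with eight intervention and eight control facilities per country. Under 5 Data collection, i, monthly counts run from six months before baseline to end-line at 24 months. Table 4 lists uptake among the primary outcomes.

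**The concern.** A power figure belongs to one contrast in one model. Here it sits beside a model that differs in three ways: it has trend terms, it has a control group, and it uses facility-level data. With only six points on each side, fitting separate trends sharply inflates the standard error of the level change, and subtracting a control series inflates it further. Pooling facilities works the other way.

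The effect size adds to the mismatch. The 2.0 is a difference between arms, but it is applied to a before/after split of 12 points.

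Uptake is a primary outcome. If the 80% is taken at face value, a null level change could be read as well-powered evidence of no effect when the planned contrast may have much less power.

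**Working it through.** **Inputs from the protocol.** Effect (200 − 100)/50 = 2.0 SD; 6+6 monthly points; autocorrelation up to 0.3; significance level 0.05, taken as two-sided; eight facilities per arm per country.

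**Assumptions for the check.** Gaussian approximation; AR(1) errors with known autocorrelation; SD of the analysed series set to 1. The variance of the estimates is (X′V⁻¹X)⁻¹. Power is the chance that a noncentral t with noncentrality 2.0/SE exceeds its critical value, with df = points minus parameters. These are best-case figures, because the autocorrelation is not estimated.

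**1. Recovering the stated 80%.** One series, intercept and level shift only, no trend:
- Autocorrelation 0: SE = √(1/6 + 1/6) = 0.577; 2/0.577 = 3.46; power 93% (normal) or 88% (t, 10 df).
- Autocorrelation 0.3: SE = 0.697; 2/0.697 = 2.87; power 82% (normal) or 74% (t).

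The stated figure is therefore matched to within two points by the no-trend mean shift with a normal reference at autocorrelation 0.3.

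**2. Adding the planned trend terms.** One series with intercept, time, level change and trend change (8 df):
- Autocorrelation 0: SE = 1.179; power 32%.
- Autocorrelation 0.3: SE = 1.202; 2/1.202 = 1.66; power 31% (38% normal).

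**3. Adding the control series.** The difference of two independent level changes has an SE √2 times as large (16 df):
- Autocorrelation 0.3: 1.202 × 1.414 = 1.70; 2/1.70 = 1.18; power 20% (22% normal).
- Autocorrelation 0: also 20%.

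Because the arms are assumed to start equal and the control to stay flat, the change of 100 is the same number whether read between arms or before/after. The numerator of 2.0 therefore carries over to the controlled contrast, but the single-series variance does not.

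**4. If SD 50 is a facility-month SD.** The mean of eight facilities with same-month correlation r has SD √((1 + 7r)/8) times as large. The article does not give r, so a range is shown. The contrast is the difference in level change from control in the level-and-trend model, at autocorrelation 0.3. The 7+24 split counts six months before baseline plus the baseline month (Month 5) as pre, and Months 6 to 29 as post. Its controlled SE before pooling is 1.470, with 54 df.

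| r | factor | SE, 6+6 | power, 6+6 | SE, 7+24 | power, 7+24 |
|---|---|---|---|---|---|
| 0 | 0.354 | 0.601 | 88% | 0.520 | 97% |
| 0.1 | 0.461 | 0.783 | 67% | 0.678 | 83% |
| 0.2 | 0.548 | 0.931 | 52% | 0.805 | 68% |
| 1.0 | 1.000 | 1.699 | 20% | 1.470 | 27% |

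The row r = 1.0 is the same as treating SD 50 as the SD of the arm series. Counting the pre-period as six months (6+24) gives 95%, 78%, 63% and 24%. None of these figures allows for variation between facilities in the size of the change, which would lower them.

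**The case against.** The strongest reply is that 31% and 20% are not the power of the model to be fitted. That model is a facility-level Poisson GEE, and the counts are framed per facility per month. The article does not say that SD 50 is the SD of an aggregated series. It presents 12 points as a requirement, whereas about 30 months are collected, and it gives a second calculation with the facility as unit. The cited simulation's model is not visible, and the stated 80% is coherent for a simple mean shift.

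Most of this stands. A reader might infer that the uptake analysis has less than half its stated power. The documents do not support that: with facility-month SD 50, low between-facility correlation and the longer series, the controlled contrast can exceed 80%. Nor can it be said that the cited simulation was misread.

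A reader might also infer that the six post-intervention points end before any effect is expected, since Table 2 anticipates change at step 7. That rests on equating those points with Months 6 to 11, which the article does not do. Step 7 also speaks of change by health services actors, not of uptake.

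The reply does not rescue the sentence as written. It names the monthly point as the unit, gives no between-facility correlation, and quotes a figure that is matched here by a model without trend terms or a control. Nor can the matter be left to an analysis plan, because the article itself states both the figure and the model.

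**Conclusion.** The point holds as a mismatch between the stated power and the planned analysis, not as proof that the study is underpowered. With one series per arm and SD 50 as the series SD, 6+6 points give about 31% power for the level change and about 20% for its difference from control. With SD 50 per facility-month and eight facilities pooled, the controlled contrast has about 20% to 88% at 6+6 and about 27% to 97% at 7+24. The deciding quantities, the meaning of SD 50 and the correlation between facilities, are not stated. All figures rest on a Gaussian approximation with known AR(1) correlation and the same change in every facility.

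**What to change.** Replace the 12-point, 80% sentence with a power figure, or a detectable rate ratio, obtained by simulating the planned controlled segmented Poisson GEE model. The simulation should use:

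- eight intervention and eight control facilities per country;
- the pre- and post-intervention months actually collected;
- autocorrelation up to 0.3;
- a stated range for same-month correlation between facilities and for variation between facilities in the change;
- a named controlled contrast: the difference in level change, in trend change, or both.

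State whether SD 50 refers to a facility-month or to an arm-level series, and define the effect on the scale of that contrast. The cost is a short simulation and possibly a less favourable stated figure; data collection does not change.

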In each country, districts were pre-selected based on similar cultural, religious and socio-economic context, as well as presence of enough health facility offering FP/C services. Data on at least 20 facilities in the pre-selected districts, where there are no social accountability intervention in FP/C currently taking place, were gathered. From the initial list, eight intervention and eight control facilities were selected based on the following criteria: provision of contraceptive services; availability of the following methods: a barrier method, a short and long-acting method, emergency contraception, and at least referral for permanent methods in districts; no social accountability programs in FP/C currently underway. Criteria that include facility type and level, average number of service users and number of new users, will be used to match the study and control facilities.

3
Study design

The study design contains two parts: capturing changes in contraceptive uptake and use (i and ii) and evaluating the effects of the social accountability intervention (iii and iv). The overview of the study design is summarized in
Table 3.

**Table 3. T3:** Study overview table.

Data gathering activity	Facility audit	Cohort study	Cross sectional survey	Process evaluation
	Changes in contraceptive uptake and use		Effects of the social accountability process	
*Outcomes*	Contraceptive uptake (new users)	Contraceptive use (method discontinuation, continuation and switching)	Social accountability intermediate outcomes (service user and health provider empowerment; expansion of negotiated space)	Dose, reach and fidelity: Process evaluation and context mapping
**Participants**	Health facilities providing FP/C services	A cohort of new users	Health Care Providers, New and continuing users of facilities women accessing FP/C services in intervention facilities	Community and district participants and staff at key program/ implementation events N.B. The context mapping activity will be undertaken in both intervention and control sites.
**Study size**	Eight intervention and eight control facilities	Estimated 800 women over eight study facilities per arm	Health care professionals (two per site) and 750 women	Four process evaluations per country tracking between 8–12 intervention related events each

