*Contraceptive use:* The discontinuation rate, being a time-to-event outcome and involving censoring, necessitates the use of sample size estimation methods for survival data. Different sample size estimates were computed for values of hazard ratio (intervention vs control) of 0.5, 0.6 and 0.7, and given values of the proportion of discontinuing use of modern contraception by end of the first year, in the control arm range from 30% to 60%. Sample size estimates were obtained using a Type I error at 5% level, accrual time of 0.01 years, and an exponential loss to follow-up of 20% that would enable a two-sided Logrank test to achieve 80% statistical power to detect the difference in discontinuation rates by the end of one year of follow-up. The final sample size was also adjusted for clustering
^40^ due to the intervention being offered at cluster level. Assuming an intra-class correlation of 0.05 and an average cluster size of 20 first users of modern contraception, resulting in a design effect of 2.0, the final sample size was doubled. The sample is estimated to be 800 women across five to eight study facilities per arm. The total sample is estimated at 1600 women distributed depending on the size of the facilities in the intervention and control arms in each country.iii. 
*Social accountability intermediate outcomes:* In intervention facilities, health care professionals providing FP/C services (two per site at pre- and at post-intervention) and 750 women aged 15 to 49 years accessing FP/C services are interviewed pre- and post- intervention over an 18-month period. Sampling for the service users survey was calculated using
*a priori* sample size calculation with the ratio of ten subjects per item ratio and guidance of more than 500 which equals a very good sample for validation
^11,
41^. The calculation is based on 75 items.iv. 

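### The cohort sample size uses a design effect of 2.0 for 20 women per facility, but the plan puts 100 or more in each (50 if 800 per arm spans both countries), so the stated 80% power does not follow.

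*Protocol article*

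**What the plan says.** All references are to the protocol article, Study design and methods.

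- **Section 4 (Sample size), item ii, Contraceptive use.** The calculation is for a "two-sided Logrank test to achieve 80% statistical power to detect the difference in discontinuation rates" at one year, with 5% type I error, accrual over 0.01 years and 20% exponential loss to follow-up. It was run for "values of hazard ratio (intervention vs control) of 0.5, 0.6 and 0.7" and for one-year discontinuation "in the control arm range from 30% to 60" per cent. The text does not say which pair gave the final figure.
- **Same item, clustering.** An ICC of 0.05 is combined with "an average cluster size of 20 first users of modern contraception, resulting in a design effect of 2.0", and the sample is doubled.
- **Same item, result.** "The sample is estimated to be 800 women across five to eight study facilities per arm". The total is given as 1600, distributed by facility size within the arms in each country.
- **Table 3, Study size, cohort column.** "Estimated 800 women over eight study facilities per arm".
- **Section 3 (Study design), item i.** There are eight intervention and eight control facilities per country.

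Table 4 in the Discussion treats the health facility as the cluster, so the cluster of 20 cannot be read as some smaller unit.

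**The concern.** The design effect depends on how many women share a cluster. The article computes it for 20 per facility, and its next statement implies at least 100. Twenty per facility would need 800/20 = 40 facilities per arm, and the study has eight per arm in each country. Nothing in the article reconciles the two figures.

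The 80% figure is the stated justification for the cohort's size, and Table 4 lists indicators of contraceptive use among the primary outcomes. If the inflation factor is too small by a factor of up to three, the plan promises more power for the discontinuation comparison than the facilities can deliver.

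**Working it through.** **Inputs from section 4, item ii.** Two-sided 5% test, 80% power, one year of follow-up, 20% exponential loss, ICC 0.05, 800 women per arm. Facility counts come from item ii, Table 3 and section 3. Equal facility sizes and a normal approximation are assumed.

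**1. Reproduce the stated design effect.** DE = 1 + (m − 1) × ICC. For m = 20: 1 + 19 × 0.05 = 1.95, given as 2.0.

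**2. Reproduce 800 per arm.** Take a hazard ratio (HR) of 0.7 and 40% control discontinuation.
- Events (Schoenfeld): 4 × (1.960 + 0.842)² / (ln 0.7)² = 246.8. Freedman's formula gives 252.0, rounded up to 253.
- Control hazard: −ln 0.6 = 0.511. Loss hazard: −ln 0.8 = 0.223.
- Event probability: λ/(λ + η) × (1 − exp(−(λ + η))), which is 0.362 in the control arm and 0.271 in the intervention arm, sum 0.633.
- Women per arm: 246.8/0.633 = 390, or 253/0.633 = 400.
- Doubled: 780 to 800.

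The neighbouring grid points at HR 0.7 miss 800 by a wide margin: about 1,050 per arm at 30% discontinuation and about 620 at 50%. HR 0.7 with 40% is therefore the grid point that reproduces 800 per arm directly. It is an inference, because the article does not name it.

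**3. Design effect at the planned cluster sizes, ICC 0.05.**

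| Reading | Women per facility | DE | Effective n per arm |
|---|---|---|---|
| 800 per arm, 8 facilities | 100 | 5.95 | 134 |
| 800 per arm, 5 facilities | 160 | 8.95 | 89 |
| 800 per arm over both countries, 16 facilities | 50 | 3.45 | 232 |
| 1600 per arm over both countries, 16 facilities | 100 | 5.95 | 269 |

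**4. Power whatever the scenario.** If the size gives exactly 80% at DE 2.0, then power = Φ(2.802 × √(2/DE) − 1.960).
- DE 5.95: Φ(1.624 − 1.960) = 37%.
- DE 3.45: Φ(2.133 − 1.960) = 57%.
- DE 8.95: Φ(1.324 − 1.960) = 26%.

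**5. Power at HR 0.7 with 40% control discontinuation.** Expected events are 800 × 0.633 = 507. Power = Φ(0.357 × √(events/DE/4) − 1.960).
- Eight facilities: 507/5.95 = 85 effective events, 38%.
- Pooled, 800 per arm: 507/3.45 = 147 effective events, 58%.
- Pooled, 1600 per arm: 170 effective events, 64%.
- Five facilities: 27%.

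**6. Power over the protocol's grid, 800 per arm at 100 per facility.**

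| HR | Control 30% | 40% | 50% | 60% |
|---|---|---|---|---|
| 0.7 | 29% | 38% | 46% | 53% |
| 0.6 | 51% | 63% | 73% | 82% |
| 0.5 | 74% | 86% | 93% | 97% |

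**7. Ceiling on information.** With k facilities per arm the effective sample cannot exceed k/ICC: 8/0.05 = 160, or 16/0.05 = 320. Both are below the 390 to 400 needed in step 2, so at that ICC more women per facility would not restore 80% power in that scenario.

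**8. ICC that would make 2.0 correct.** (2 − 1)/99 = 0.010 at 100 per facility, and 1/49 = 0.020 at 50.

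**The case against.** The strongest reply is that the size of the loss is not fixed by the article. This stands in several respects.

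- **The effect behind 800 is not stated.** A reader might infer that the protocol claims 80% power for HR 0.7. It lists three hazard ratios and a range of control rates and ties 800 to none of them. HR 0.6 with 40% control discontinuation doubles to about 400 per arm, which sums to about 800 over two countries. On that reading a pooled analysis at 50 per facility still has about 85% power for HR 0.6.
- **A single figure of 38% is not the result.** It holds for eight facilities of 100 at HR 0.7 with 40% discontinuation. Over the grid the range at 100 per facility is 29% to 97%.
- **The scope of 800 is ambiguous.** Table 3 and item ii point to 100 or more per facility. The sentence on the total of 1600 can be read per country or overall, and the overall reading gives 50. The five-facility case matters little, because section 3 and Table 3 fix eight.
- **The uptake calculation is not further evidence.** A reader might see a conflict between 20 women and "between 100 and 200 new users per facility, per month" in item i. That range concerns monthly facility figures for another outcome. A facility of that volume could still contribute 20 women to a cohort.
- **The analysis is not invalidated.** Section 6 plans marginal Cox and/or shared frailty models with 95% confidence intervals. A reader might infer that a null result would be taken as evidence of no effect, but the article does not say so. The models account for clustering, though they do not supply the missing power.

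The inconsistency itself has no answer in the text. Under every reading of 800 the women per facility exceed 20 by at least a factor of 2.5.

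**Conclusion.** The point holds as an internal arithmetic error in the sample-size justification. At the protocol's own ICC, the design effect is 5.95 for 100 women per facility, or 3.45 if 800 per arm spans both countries, not 2.0. A design sized to 80% at 2.0 then has about 37% or 57% power respectively. At the grid point that reproduces 800 (HR 0.7, 40% control discontinuation), power is about 38% per country, 58% pooled with 800 per arm and 64% pooled with 1600 per arm.

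For HR 0.7 over 30% to 60% control discontinuation, power at 100 per facility is 29% to 53%. HR 0.5 with control discontinuation of 40% or more, and HR 0.6 at 60%, still exceed 80%. The cohort is therefore not incapable of detecting any effect.

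Unequal facility sizes would lower power further. So would a t reference with 14 degrees of freedom, to about 34% in the 38% case.

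**What to change.** In section 4, item ii:

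1. Recompute the design effect with the planned number of women per facility.
2. State the hazard ratio and control discontinuation rate behind 800, and whether 800 per arm is per country or overall. Align Table 3 with the answer.
3. Replace the 80% claim with what the design gives. At ICC 0.05 and 80% power, the detectable hazard ratio over 30% to 60% control discontinuation is about:
   - 0.47 to 0.61 per country, with 800 per arm in eight facilities;
   - 0.57 to 0.69 pooled, with 800 per arm in 16 facilities;
   - 0.60 to 0.71 pooled, with 1600 per arm in 16 facilities.
4. Alternatively, keep 2.0 and state and justify the smaller ICC it requires, about 0.01 at 100 per facility.

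Whether the per-country or the pooled analysis carries the inference is a choice that may sit in the statistical analysis plan, and is not requested here. The change is to wording and figures only, with no extra enrolment. Its cost is a less favourable stated power.
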